## 2. Research Background and Scientific Rationale

Pediatric acute myeloid leukemia represents a heterogeneous group of hematologic malignancies characterized by clonal proliferation of myeloid precursors with impaired differentiation. Despite significant advancements in risk-adapted therapy approaches, including allogeneic hematopoietic stem cell transplantation for high-risk patients, relapse remains the predominant cause of treatment failure, with 5-year event-free survival rates plateauing at approximately 50-60% in contemporary clinical trials. Minimal residual disease monitoring has emerged as a critical component of modern risk stratification in acute leukemias. Among various MRD detection methodologies, multiparametric flow cytometry-based MRD assessment offers the advantage of rapid turnaround time, widespread availability, and applicability to nearly all patients regardless of genetic markers. The conventionally accepted threshold of 0.1% for defining MRD positivity has demonstrated prognostic utility across multiple studies, yet evolving technological capabilities in flow cytometry warrant reevaluation of this standard. Recent evidence suggests that lower levels of residual disease, previously classified as MRD-negative by the 0.1% threshold, may still harbor significant prognostic implications. Technological advancements now enable reliable detection of leukemic cells at levels as low as 0.01%, raising important questions about the optimal threshold for clinical decision-making. This study addresses a critical evidence gap by systematically evaluating a lower MRD threshold in a large, well-annotated pediatric AML cohort.

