### 3.2 Secondary Objectives

1. To validate the consistency of the proposed 0.05% MRD threshold across established genetic risk subgroups (low-risk, standard-risk, high-risk).
2. To establish the independent prognostic value of the novel MRD threshold through multivariate Cox regression analysis adjusting for known clinical and molecular variables.
3. To assess the clinical utility of the lower threshold in guiding treatment decisions, particularly regarding transplantation candidacy.

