### 3.3 Research Hypotheses

- **Primary Hypothesis**: An MRD threshold of 0.05% provides superior prognostic discrimination compared to the conventional 0.1% threshold for predicting 5-year EFS in pediatric AML.
- **Secondary Hypothesis**: The 0.05% threshold demonstrates consistent prognostic performance across all genetic risk categories and offers significant net reclassification improvement.

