### 5.3 Sample Size Justification

The initial TARGET-AML cohort included 1,205 pediatric patients with non-M3 AML. Based on power calculations for detecting a hazard ratio of 2.0 for EFS with 80% power at α=0.05, the available sample size provides adequate statistical power for the proposed analyses. The cohort characteristics demonstrate balanced representation across key prognostic subgroups.

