### 6.3 Variable Definitions

- **Event-free survival (EFS)**: Time from diagnosis to first event (induction failure, relapse, secondary malignancy, or death from any cause)
- **MRD positivity**: Defined using two thresholds: traditional (≥0.1%) and novel (≥0.05%)
- **Complete remission**: <5% blasts in morphologically normal bone marrow with recovery of peripheral counts
- **Genetic risk groups**:
  - Low risk: inv(16)/t(16;16) or t(8;21)
  - High risk: monosomy 7 or del(5q)
  - Standard risk: All other cases with adequate cytogenetic data

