### 7.2 Secondary Analyses

**Cox Regression**: Univariate and multivariate Cox proportional hazards models will assess the association between MRD thresholds and EFS, adjusting for relevant covariates. **Net Reclassification Improvement**: Categorical NRI will quantify improvement in risk prediction using the novel threshold. **Subgroup Analysis**: Consistency of the MRD threshold will be evaluated within predefined genetic risk categories.

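### Consistency of the 0.05% threshold across genetic risk groups is claimed, but the stated analysis looks only within each group and does not estimate any difference between groups

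*Protocol*

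**What the plan says.** The secondary hypothesis in Protocol section 3.3 reads: "The 0.05% threshold demonstrates consistent prognostic performance across all genetic risk categories and offers significant net reclassification improvement". Secondary objective 1 in section 3.2 sets out to validate that consistency across the low-, standard- and high-risk groups. The method is a single sentence in section 7.2: "Consistency of the MRD threshold will be evaluated within predefined genetic risk categories". Sections 7.1 to 7.3 name no interaction term, heterogeneity test, ratio of hazard ratios or definition of consistent.

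Section 6.3 defines the groups. Low risk is the two core-binding-factor lesions, high risk is monosomy 7 or del(5q), and standard risk is every other case with adequate cytogenetics. No group sizes are given.

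Section 5.3 justifies the sample size with one effect: "Based on power calculations for detecting a hazard ratio of 2.0 for EFS with 80% power at α=0.05". It concludes that the available sample is adequate for the proposed analyses and adds, without counts: "The cohort characteristics demonstrate balanced representation across key prognostic subgroups".

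**The concern.** Consistency across groups is a statement about differences between groups. A result within one group reflects both the size of the effect and the amount of information there. A non-significant hazard ratio may only mean few events, and three significant hazard ratios may differ widely. The analysis in 7.2 therefore does not answer the question in 3.2 and 3.3.

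Section 5.3 hides the difficulty. Its power statement concerns one hazard ratio in the whole cohort, yet it is extended to all proposed analyses, and subgroup balance is asserted without a number.

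At stake is a secondary conclusion about where the lower threshold may be used. The error can go either way: a uniform effect may be reported as inconsistent, or a materially different effect as consistent.

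**Working it through.** **Inputs from the protocol.** Hazard ratio 2.0, 80% power and α = 0.05 (section 5.3; sidedness not stated, two-sided taken). N = 1,205 is an upper bound for the analysis set, since section 5.3 calls it the initial cohort. The overall event fraction is 40-50% by 5 years, from "5-year event-free survival rates plateauing at approximately 50-60% in contemporary clinical trials" in section 2.

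**Assumed inputs (none in the protocol).** Low risk 25%; high risk 3%, 5%, 8% or 10%; standard risk the remainder. Five-year event fractions 30/50/65% and MRD ≥0.05% in 20/30/45% for low/standard/high. As the contrary case: equal thirds with 40-50% events and 20-50% MRD-positive in every group.

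**Step 1: the protocol's own power claim.** Events needed = (1.960 + 0.842)² / [a(1−a)(ln 2)²], where a is the MRD-positive share. This gives 66 events at a = 0.5, 78 at 0.3 and 103 at 0.2. At 40-50% events that is 132 (66/0.5) to 258 (103/0.4) patients. With 1,205 patients the power exceeds 99.9%, so section 5.3 is right about the pooled hazard ratio.

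**Step 2: reading each group by p<0.05 when the true hazard ratio is 2.0 in all three.** With d events in a group, power = Φ(ln 2 × √[d·a(1−a)] − 1.960). Example, 5% high risk: 60 patients, 39.2 events, d·a(1−a) = 39.2 × 0.45 × 0.55 = 9.69, and power = Φ(0.693 × 3.11 − 1.960) = 0.58. Groups are independent, so the probability that all three are significant is the product of the three powers.

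| High-risk share | High-risk patients | Power low / standard / high | All three significant | At least one not |
|---|---|---|---|---|
| 3% | 36 | 0.75 / 1.00 / 0.39 | 29% | 71% |
| 5% | 60 | 0.75 / 1.00 / 0.58 | 43% | 57% |
| 8% | 96 | 0.75 / 1.00 / 0.78 | 58% | 42% |
| 10% | 120 | 0.75 / 1.00 / 0.86 | 65% | 35% |
| Equal thirds | 402 | 0.94 to 0.998 in each | 83% to 99.5% | 0.5% to 17% |

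A 2-df interaction test would falsely signal a difference in 5% of studies in each row.

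**Step 3: the opposite error.** Take equal thirds with true hazard ratios of 2, 2 and 4. All three groups are significant in about 88% of studies (40% events, 20% MRD-positive) to 99.7% (50% events, 50% MRD-positive). A 2-df heterogeneity test detects this difference with about 73% to 96% power over the same range.

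**Step 4: how much information a high-risk group would need.** For 80% power at hazard ratio 2.0, the events from step 1 divided by event fractions of 50-70% give 95 (66/0.7) to 156 (78/0.5) high-risk patients at 30-50% MRD-positive. For the ratio of hazard ratios, high against standard, SE = √(1/w_high + 1/w_std) with w = d·a(1−a). At 5% high risk this is √(1/9.69 + 1/88.57) = 0.338, so the 95% interval runs a factor of exp(1.96 × 0.338) = 1.9 either way. At 3% the factor is 2.3 and at 10% it is 1.6.

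**Step 5: limits of the interaction test.** If the true high-risk hazard ratio is 1.0 and the others are 2.0, the 2-df test has power of about 29%, 44%, 62% and 70% at high-risk shares of 3%, 5%, 8% and 10%.

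**The case against.** The protocol sets no rule that each group must reach p<0.05. Section 7.2 is equally compatible with reporting a hazard ratio and interval per group and comparing them by eye. Consistent performance need not mean equal hazard ratios. An interaction term is often left to a separate analysis plan, and section 10.2 refers to a pre-specified one. All subgroup inputs are assumed, and the only thing the protocol says about subgroup sizes is that they are balanced; in that case false inconsistency is uncommon. The interaction test is itself weak when one group is small.

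Much of this stands, and it rules out three stronger readings that a reader might infer:

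- *The protocol would often declare a uniform effect inconsistent.* This needs both a significance rule and a small high-risk group, and the protocol states neither.
- *The high-risk group cannot support the claim.* The two-lesion definition makes a small group plausible, but no count is given, and about 95-156 patients would suffice for a hazard ratio of 2.0.
- *An interaction test has been ruled out.* It is simply not named.

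What does not stand is the defence that this is only missing detail. The protocol does state a method, and that method addresses a different question from the hypothesis. If a separate plan adds an interaction model, 7.2 still has to be aligned with it. Equal groups do not rescue the method either, because they only make the opposite error the likely one (step 3).

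**Conclusion.** The concern holds in limited form. Sections 3.2 and 3.3 make a between-group claim, and 7.2 provides only within-group evaluation, with no measure of difference and no definition of consistent. This mismatch does not depend on any assumed number.

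The consequences in the working are conditional on reading the groups by significance and on the assumed shares, event fractions and MRD-positive proportions. They show that such a reading misleads with small and with equal groups alike, not that this study will reach a wrong answer. At a common hazard ratio of 1.5, at least one group would be non-significant in about 65% (equal thirds, 45% events, 30% MRD-positive) to 95% (3% high risk) of studies.

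Section 5.3 is correct for the pooled hazard ratio of 2.0. Nothing in the protocol supports extending it to the subgroups, or supports the balance statement. Restricting hypothesis 3.3 in advance would be premature without the counts. The point should be addressed before analysis; it touches a secondary objective, not the primary comparison of 0.05% with 0.1%.

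**What to change.** **Section 7.2.** Fit one Cox model for EFS in the whole cohort with MRD status, genetic risk group and their interaction. Report the interaction test, the hazard ratio with 95% CI in each group, and the ratio of hazard ratios against standard risk with 95% CI. State in advance that consistency will be judged from those ratios and intervals, and how wide a departure would still count as consistent. Neither per-group p-values nor a non-significant interaction alone should decide it.

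**Section 5.3.** Replace the balance sentence with the number of patients, events and patients with MRD 0.05% to <0.1% in each risk group. The last count matters because only those patients change class between the two thresholds. If they were 3-8% of a high-risk group of 36 to 120 patients, there would be about 1 to 10 of them (36 × 0.03 = 1.1; 120 × 0.08 = 9.6). State that the adequate-power claim applies to the pooled hazard ratio of 2.0.

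**Conclusion drawn under 3.3.** Treat high risk as descriptive only if the observed counts leave its ratio of hazard ratios too imprecise.

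**Cost.** A few lines of protocol text and one model on existing data. The price is a more modest claim: the limited power in step 5 means that a small high-risk group may leave the question open, and the report would have to say so.

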### 7.3 Sensitivity Analyses

- Multiple imputation for missing data
- Landmark analysis at 3 months post-induction
- Competing risks analysis considering non-relapse mortality

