## 5. Study Population

### 5.1 Inclusion Criteria

- Pediatric patients (<18 years at diagnosis) with newly diagnosed de novo AML (non-M3 subtype)
- Availability of MFC-MRD data measured after completion of Induction Course 1 and/or Course 2
- Treatment according to one of the specified protocols: AAML03P1, AAML0531, or AAML1031
- Complete baseline clinical and molecular characterization data
- Minimum follow-up duration of 36 months for surviving patients

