### 5.2 Exclusion Criteria

- Acute promyelocytic leukemia (M3 AML) patients
- Patients with incomplete MRD data or key prognostic variables
- Secondary AML or therapy-related AML cases
- Patients with insufficient follow-up data

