### 6.4 Data Quality Assurance

- Double data entry for key variables with discrepancy resolution
- Range checks for continuous variables
- Consistency checks across related variables
- Missing data assessment and appropriate handling strategies

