### 10.2 Mitigation Strategies

- Regular security audits
- Pre-specified statistical analysis plan
- Sensitivity analyses for missing data
- Peer review of analytical methods

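### Eligibility requires complete baseline, molecular and key prognostic data, so the planned multiple imputation cannot test missing covariates; the MRD criteria also conflict for patients with one course measured

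*Protocol*

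**What the plan says.** Three parts of the protocol bear on missing data.

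- **Eligibility.** Section 5.1 requires "Complete baseline clinical and molecular characterization data" and "Availability of MFC-MRD data measured after completion of Induction Course 1 and/or Course 2". Section 5.2 excludes "Patients with incomplete MRD data or key prognostic variables" and "Patients with insufficient follow-up data". The term key is not defined.
- **Missing-data analyses.** Section 7.3 lists "Multiple imputation for missing data" among the sensitivity analyses, without naming a cohort or variables. Section 10.2 offers "Sensitivity analyses for missing data" as a mitigation. Section 6.4 adds only "Missing data assessment and appropriate handling strategies".
- **What the analyses use.** Section 7.1 specifies Kaplan-Meier curves and log-rank tests by MRD status, and a ROC analysis of MRD against 5-year EFS status. Covariates enter in 7.2, through the adjusted Cox model and the genetic risk subgroups.

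The figure of 1,205 has two meanings. Section 1 gives it as the number with complete MRD data. Sections 4.5 and 5.3 place it before the eligibility criteria are applied.

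**The concern.** A missing-data sensitivity analysis should show whether the conclusion depends on leaving out patients whose data are incomplete. Here those patients leave at eligibility, before any analysis. The main analysis is therefore complete-case by selection for baseline and molecular covariates, and the analysis named as the safeguard is confined to the same selected patients.

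Two consequences follow. First, a patient with known MRD and known EFS is dropped from the survival curves and the ROC analysis for lack of, say, a WT1 result that neither uses. If completeness of typing is related to treatment era, treatment protocol or early clinical course, the threshold comparison is made in a selected group. The data span September 1996 to December 2016 and three treatment protocols (4.2, 5.1), so this is plausible, although the document does not show it.

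Second, the MRD criteria do not agree on patients with one course measured. The two readings give different cohorts for the first primary objective, which concerns both Course 1 and Course 2.

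**Working it through.** The protocol states no figure to reproduce on this point: 1,205 is an available cohort, and no missingness rate is given. The check is mainly a comparison of sections.

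**Step 1. What can still be missing among eligible patients?**

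| Data | Rule | Can it be missing? |
|---|---|---|
| Baseline clinical and molecular | 5.1 requires complete data | No |
| Key prognostic variables | 5.2 excludes if incomplete | No |
| MRD at the other course | 5.1 accepts one course; 5.2 excludes incomplete MRD | Depends on which governs |
| Post-baseline items outside the key set (6.1: response after each course, transplant details) | None, unless counted as key | Possibly |

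The first two rows hold the covariates for which imputation would matter in the adjusted Cox model. Both are closed. No section says that imputation would be run in a wider cohort.

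**Step 2. Who is removed from 7.1 without need?** Kaplan-Meier, log-rank and ROC need an MRD value and EFS. Any patient who has both but fails a baseline or molecular requirement is lost to all three. NRI is left out of this list because 7.2 does not say whether its risk model includes covariates.

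**Step 3. The one-course conflict.** Section 6.3 counts EFS from diagnosis and includes induction failure and death as events. A patient who dies after the Course 1 sample and before a Course 2 sample has no Course 2 value. If 5.1 governs, this patient is in the Course 1 analysis. If 5.2 governs, the patient is out because of an early event, and the Course 1 cohort is conditioned on reaching a Course 2 sample. That is selection on the outcome.

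**Step 4. Scale, on assumed rates.** Section 6.1 lists five genetic items (karyotype, FLT3-ITD, NPM1, CEBPA, WT1). Let each be missing in a proportion m of patients. Under independence the complete share is (1 − m)^5. If the same patients lack all five, the loss is only m.

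| m (assumed) | Complete share, independent | Lost of 1,205, independent | Lost of 1,205, full overlap |
|---|---|---|---|
| 3% | 0.97^5 = 0.859 | 170 | 0.03 × 1,205 = 36 |
| 5% | 0.95^5 = 0.774 | 273 | 0.05 × 1,205 = 60 |
| 10% | 0.90^5 = 0.590 | 493 | 0.10 × 1,205 = about 120 |

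**Step 5. Is power the problem?** Section 5.3 uses a hazard ratio of 2.0, 80% power and α = 0.05. By Schoenfeld's formula, power = Φ(√(D·p(1 − p)) × ln 2 − 1.96), with D events, MRD-positive share p and a two-sided test. Assume a 45% event rate, p = 0.20 and only 30% of patients kept. Then D = 1,205 × 0.30 × 0.45 = 163, √(163 × 0.16) = 5.10, 5.10 × 0.693 − 1.96 = 1.58, and power is 0.94. With p = 0.10 it is 0.76. Only the combination of heavy loss and a small positive group brings power below 80%.

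**The case against.** A reader might infer that the imputation has nothing at all to work on and will reproduce the primary result exactly. The document does not support that. If 5.1 governs, the other course's MRD can be missing and could be imputed. Fields outside the undefined key set may have gaps. With "Minimum follow-up duration of 36 months for surviving patients", 5-year status can also be unknown for survivors followed for 36 to 60 months. None of this reaches missing baseline or molecular covariates.

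A second defence is that 7.3 is a single line and its cohort could be set in a separate analysis plan: complete-case as main analysis, imputation over a wider cohort as sensitivity. That is a coherent design and may be what was meant. But eligibility is fixed in this protocol, and an analysis plan cannot return excluded patients to the study without contradicting it. The conflict is in the text as it stands.

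Third, the completeness criteria have a purpose. The genetic subgroups and the adjusted model need these data, 6.3 limits standard risk to cases with adequate cytogenetics, and one common population keeps unadjusted and adjusted results comparable. This stands: it would be wrong to say that patients are lost for no gain. It justifies completeness for those analyses, not for the survival curves and the ROC analysis.

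Fourth, the losses in the working rest on assumed rates. This also stands. The document shows neither how many patients are lost nor that completeness is related to outcome, and it gives no count for the 0.05% to 0.1% band, so no loss there can be stated.

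**Conclusion.** The point holds in limited form. Followed as written, 5.1 and 5.2 prevent the imputation in 7.3, and the mitigation in 10.2, from testing sensitivity to missing baseline or molecular covariates. The same criteria remove patients from Kaplan-Meier, log-rank and ROC analyses that do not use those covariates. Sections 5.1 and 5.2 also conflict on patients with one course measured, and if 5.2 prevails the Course 1 cohort is selected partly on early events.

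These conclusions rest on the wording alone. The size of any bias is unknown. Under the assumed rates of 3% to 10% per genetic item, the loss runs from 36 patients (3%, full overlap) to 493 (10%, independence). The matter is selection and a safeguard that misses its target; overall power for a hazard ratio of 2.0 is largely unaffected under the assumptions shown.

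**What to change.** 1. In 5.1 and 5.2, replace the MRD wording with one rule: an evaluable quantitative MRD value at the course being analysed. Define one analysis set for Course 1 and one for Course 2.
2. Replace the baseline and molecular completeness criteria, and the key-variable exclusion, with requirements specific to each analysis: genetic risk classifiable under 6.3 for the subgroups, and the named covariates for the adjusted Cox model.
3. Run Kaplan-Meier, log-rank and ROC on all MRD-evaluable patients in the set for that course.
4. In 7.3, state that the Cox covariates are imputed in that wider set and reported beside the complete-case model. Which of the two is called main is a matter of choice; the protocol should say which.
5. Compare patients with and without complete covariates on treatment protocol, period, MRD and EFS.

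The cost is a few lines of eligibility and analysis text. The data already exist, so no new collection is needed and the unadjusted analyses can only gain patients. The small downside is that unadjusted and adjusted analyses may have different denominators, which should be reported with each result. The change should be made before extraction fixes the cohort.

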### 7.4 Statistical Software

- Primary analysis: R software (version 4.1.0)
- Secondary analysis: SPSS (version 26.0)
- Sample size justification: Power analysis using PASS software

